### Statistical Analysis

Descriptive statistics will be calculated for all outcome measures. Differences in categorical variables between groups will be analysed using a Chi Square Test. A one way ANOVA with Student-Newman-Keuls test will be used for Post-hoc comparisons for all continuous normally distributed data.

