### Participants

One hundred and fifty consenting male and female subjects, aged 18-65 years will be recruited comprising three equal groups of (1) Patients with NSAP, (2) Patients with cervical radiculopathy and (3) Age and gender matched controls.

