#### • Groups 1 and 2: NSAP and Cervical Radiculopathy subjects

##### Inclusion criteria

All participants from patient groups will be office workers who have significant unilateral upper limb pain as defined by a numerical rating score of ≥ 3/10 [31,41], who spend more than 40% of their working week using desktop equipment [24] and have been in their current employment or similar (i.e. involving office work/keyboard operation) for at least two years [34]. More specific information regarding diagnostic criteria for each patient group is outlined in the next section. Patients will be recruited from local orthopaedic outpatient and occupational health departments of Dublin hospitals and physiotherapy practices and also from the staff and student population of University College Dublin.

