#### • Group 3: Control Subjects

##### Inclusion criteria

Fifty age and gender matched subjects will be included if they have no history of significant neck, scapular or shoulder pain over the past 12 months (significant pain is defined as pain ≥ 3/10 on a visual analogue scale [31,41] and do not use desktop equipment for more than 40% of their working week [24]. The control group will be recruited from staff/students at University College Dublin, St Vincent's University Hospital staff and the local community.

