### Group Selection

#### Screening and Allocation to study groups

Participants will be interviewed and screened for general inclusion and exclusion criteria (Figure 1: Study Protocol). Participants with cervical radiculopathy will be recruited from a local spinal surgery service and identified by the presence of radicular pain in the upper limb, positive upper limb neurodynamic tests, Spurling's test, and Valsalva manoeuver as well as MRI confirmation of nerve compression [42,43]. The MRI scans of all patients will be reviewed by a radiologist and those patients with evidence of intervertebral disc protrusion and associated nerve root compression will be identified. Nerve root compression will be classified as absent, minimal, moderate or severe [44].

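### The planned one-way ANOVA has no age or sex term, so the NSAP versus radiculopathy comparison is open to confounding by both

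*Protocol article*

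**What the plan says.** Protocol article, Statistical Analysis, names two tests. For continuous, normally distributed outcomes: "A one way ANOVA with Student-Newman-Keuls test will be used for Post-hoc comparisons for all continuous normally distributed data". For categorical ones: "Differences in categorical variables between groups will be analysed using a Chi Square Test". No covariate, stratum or matched-set term appears.

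Participants describes "three equal groups of (1) Patients with NSAP, (2) Patients with cervical radiculopathy and (3) Age and gender matched controls", with the eligible population given as "One hundred and fifty consenting male and female subjects, aged 18-65 years will be recruited". The control criteria (Group 3) repeat the matching: "Fifty age and gender matched subjects will be included". Neither section says which patient group the controls are matched to, or whether matching is by individual or by frequency. No section describes matching the two patient groups to each other.

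On sources, Screening and Allocation to study groups says "Participants with cervical radiculopathy will be recruited from a local spinal surgery service". The inclusion criteria for Groups 1 and 2 together say "Patients will be recruited from local orthopaedic outpatient and occupational health departments of Dublin hospitals and physiotherapy practices" and add the university's staff and students.

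The last objective is to compare NSAP profiles with those of radiculopathy patients and controls. The hypothesis at the end of Background is that some NSAP patients will present like radiculopathy patients.

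**The concern.** By matching controls on age and gender, the design treats both as variables that can affect the outcomes. The named analysis then leaves both out. The gap matters most for NSAP versus radiculopathy, where no matching is described.

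In an unadjusted comparison, a difference in age or sex make-up passes straight into the group difference. It could look like a somatosensory difference, or it could hide one. Hiding one matters here because the hypothesis concerns similarity. The chi-square test might reveal a sex imbalance but would not adjust for it. Study Limitations acknowledges bias from having one assessor and the lack of MRI or nerve conduction studies in NSAP, but not age or sex imbalance.

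**Working it through.** **The plan's own figures.** Sample size/power calculation gives 50 per group, effect size 0.5, power 0.8 and two-tailed α 0.05. The two-sided normal formula gives n = 2(1.96 + 0.84)²/0.5² ≈ 63 per group. Power at 50 is Φ(0.5/√(2/50) − 1.96) = Φ(0.54) ≈ 0.705. The stated 50 therefore does not reproduce two-sided. That is a separate matter; only n = 50 per group and the 0.5 SD target are used below.

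**Bias.** Let d be the difference in mean age between the patient groups, in SD of age, and ρ the within-group correlation of age with the outcome. The unadjusted group difference is then shifted by ρ·d SD. The article gives neither quantity. Assumed examples:
- ρ = 0.2, d = 0.5: bias 0.1 SD
- ρ = 0.2, d = 1.0: bias 0.2 SD
- ρ = 0.5, d = 0.8: bias 0.4 SD, close to the 0.5 SD target

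**Effect on the planned test.** With three groups of 50 and 147 error degrees of freedom, Student-Newman-Keuls first compares the largest and smallest means against q(3) = 3.35. Adjacent means are tested against q(2) = 2.79 only if that first step is significant. In SD units the critical gaps are 3.35/√50 = 0.474 and 2.79/√50 = 0.395. A two-group t-test uses 1.98 × √(2/50) = 0.397. So the chance of declaring NSAP and radiculopathy different depends on where the controls lie.

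Rejection of NSAP = radiculopathy when there is no true difference (Student-Newman-Keuls columns by simulation, 40,000 runs per setting):

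| Bias (SD) | Controls at or between patient means | Controls about 0.5 SD beyond the nearer patient mean | Two-group t-test |
|---|---|---|---|
| 0 | about 2.5% | about 5% | 5% |
| 0.1 | about 4% | about 8% | 7.9% |
| 0.2 | about 10% | about 17% | 16.8% |
| 0.4 | 38–41% | about 51% | 50.8% |

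When controls lie well apart, the first step is nearly always passed and the procedure behaves like a t-test. When they do not, the first step gives some protection, but rejection still rises well above its no-bias level.

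**Precision after adjustment.** With age in a linear model, the standard error of the patient contrast is √[(1 − ρ²)(2/50)(1 + d²/4)], and power for 0.5 SD is Φ(0.5/SE − 1.96).
- ρ = 0.2, d = 1.0: SE = √(0.96 × 0.04 × 1.25) = 0.219, power 0.63
- ρ = 0.5, d = 0.25: SE = √(0.75 × 0.04 × 1.016) = 0.175, power 0.82

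Over ρ = 0.2–0.5 and d = 0.25–1.0, power runs from 0.63 to 0.82, against 0.705 unadjusted with no imbalance. Under a linear age effect the bias is removed throughout, but precision can move either way.

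**The case against.** The strongest reply is that this is a short summary in a journal article. Covariates are often left to an analysis plan, which is not shown and might contain adjustment. That stands as far as it goes. But a one-way ANOVA is by definition a single-factor analysis, so the article names a method that excludes age and sex rather than leaving the matter open.

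A reader might infer that the NSAP–radiculopathy comparison is confounded and the groups not matched at all. The document does not support that. It gives no age or sex distribution by group and does not say how controls are matched. If one control group were frequency-matched to both patient groups, those groups would be indirectly similar. Both also share the age range, the office-work and pain criteria, and the exclusions. These restrictions do not balance age or sex, but they count against calling the groups unlike.

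A reader might also infer a clean split of sources, with spinal surgery for radiculopathy and the rest for NSAP. The Groups 1 and 2 criteria list orthopaedic outpatient, occupational health, physiotherapy and university sources for both groups. Only the spinal surgery service is specific to radiculopathy.

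Nor should the 8%, 17% and 51% be read as the plan's error rates. They need controls well apart from both patient groups. A claim that adjustment simply raises power would assume balance, which is the opposite of the situation that creates bias.

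Finally, the hypothesis concerns a subset of NSAP patients and the comparison is the last of four objectives. That lowers the weight of the point, but the comparison remains a stated objective.

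**Conclusion.** The point holds as a mismatch between design and named analysis: age and gender are design variables for the controls, the analysis omits them, and the NSAP–radiculopathy contrast is open to confounding by both. Actual confounding is not shown.

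Its size cannot be known from the article. For an assumed bias of 0.1–0.4 SD and no true difference, rejection is about 4% to 41% if controls lie at or between the patient means, and about 8% to 51% if they lie about 0.5 SD away. The ranges rest on normal outcomes, equal variances, 50 per group and the assumed biases. The plan should be changed because the remedy is cheap, not because a particular bias has been demonstrated.

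**What to change.** Replace the one-way ANOVA with a linear model (ANCOVA) containing group, age as a continuous variable, and sex. Report the three adjusted pairwise differences with 95% confidence intervals, using a comparison procedure that controls multiplicity over the three pairs.

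No new data should be needed: age is an eligibility variable, and both age and gender are needed for the matching. The recruitment of controls need not change. The model spends two degrees of freedom. If the groups differ in age or sex, the adjusted contrast also loses some precision. Precision improves only if the groups are roughly balanced and age and sex explain outcome variance.

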Clearly, there is much debate as to whether NSAP, which appears to have features of neuropathic pain, is indeed a neuropathic disorder. Furthermore, there are currently no gold standards with which to classify pain as definitively neuropathic. The purpose of this study is to comprehensively describe the somatosensory profiles in patients with NSAP and to compare them to somatosensory profiles in asymptomatic subjects and subjects with cervical radiculopathy. It is hypothesised that some of the NSAP group may demonstrate a similar presentation to that of cervical radiculopathy, indicating a probable neuropathic pain presentation.

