## Methods/Design

### Objectives

The objectives of this study are to:

• Describe the somatosensory profiles of subjects with NSAP in terms of neurological examination, qualitative measures of pain, neural tissue provocation tests and QST.

• Describe impairment and disability associated with NSAP by means of the Disabilities of the Arm, Shoulder and Hand (DASH) and SF-36 questionnaires.

• Investigate for correlations between clinical examination findings, QST profiles and questionnaire derived pain profiles in subjects with NSAP.

• Compare somatosensory profiles of subjects with NSAP to those with cervical radiculopathy and asymptomatic controls.

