### Sample size/power calculation

Power analysis: Sample size was calculated based on mean and standard error vibration threshold data from a study by Greening et al., (2003). A sample of size of 50 patients with NSAP, 50 patients with cervical radiculopathy and 50 matched control subjects will be required to detect a medium effect size (0.5) with 0.8 power and 0.05 two tailed significance level.

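### Student-Newman-Keuls pools one variance over all three groups on the sole condition of normality; an unequal-variance procedure would be safer at almost no cost

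*Protocol article*

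**What the plan says.** The Statistical Analysis section fixes the comparison of continuous outcomes in one sentence: "A one way ANOVA with Student-Newman-Keuls test will be used for Post-hoc comparisons for all continuous normally distributed data". It does not mention equality of variances or an unequal-variance alternative.

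The Sample size/power calculation section sets equal groups: "A sample of size of 50 patients with NSAP, 50 patients with cervical radiculopathy and 50 matched control subjects". It works from published vibration-threshold data but prints no standard deviation for any group.

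The Objectives section asks the study to "Compare somatosensory profiles of subjects with NSAP to those with cervical radiculopathy and asymptomatic controls", without ranking one comparison above the other. The hypothesis that closes the Background is that "some of the NSAP group may demonstrate a similar presentation to that of cervical radiculopathy, indicating a probable neuropathic pain presentation".

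**The concern.** The standard Student-Newman-Keuls test divides every pairwise difference by a standard error built from the ANOVA error mean square, so the third group's variance enters a comparison to which it does not belong. Equal group sizes make the overall F test fairly robust, but they do not repair this.

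The article gives two reasons to think that spread may differ between groups:

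- **NSAP.** If only some NSAP participants resemble radiculopathy, the NSAP group is a mixture and should be more variable than a homogeneous group.
- **Radiculopathy (an inference).** Screening and Allocation requires disc protrusion with nerve root compression but states no root level. Thermal Testing and Vibration thresholds measure everyone at fixed C6, C7 and C8 hand sites. At a given site some patients would have the affected root and others would not.

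If controls are less variable than patients, they shrink the standard error of the NSAP-radiculopathy comparison, which then rejects too often. The same rule governs every continuous, normally distributed outcome.

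**Working it through.** **Inputs.** From the article: n = 50 per group, Student-Newman-Keuls after one-way ANOVA, two-sided 5%, standardised effect 0.5. Assumed, because no SDs are given: control SD = 1 and patient SD = k, with k from 1 to 2. Error degrees of freedom are 150 − 3 = 147.

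**The plan's own figure.** Two groups, effect 0.5, two-sided 5% and 80% power need 2 × (1.960 + 0.842)² / 0.5² ≈ 63 per group; at 50 per group power is about 0.70. The stated 50 is therefore not reproduced. That is a separate matter; only n = 50 and the effect of 0.5 are used below.

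**Pooled variance against the variance the pair needs**

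- Both patient groups at SD k: pooled (2k² + 1)/3. NSAP-radiculopathy needs k², which is larger. NSAP-control needs (k² + 1)/2, which is smaller.
- Only NSAP at SD k: pooled (k² + 2)/3. Both NSAP comparisons need (k² + 1)/2, which is larger.

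At k = 1.5 the first case gives 1.833 pooled against 2.25 and 1.625; the second gives 1.417 against 1.625.

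**False rejection, NSAP versus radiculopathy, equal means, controls well separated.** The two patient groups are then adjacent in rank and the three-group step is always passed, so the rate is approximately 2 × [1 − Φ(1.976 × √(pooled / needed))]. For k = 1.5 with both groups inflated: √(1.833/2.25) = 0.903, 1.976 × 0.903 = 1.784, rate 7.4%. Simulated values (100,000 trials each):

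| k | Both: formula | Both: simulated | Only NSAP: formula | Only NSAP: simulated | Gated Welch, simulated |
|---|---|---|---|---|---|
| 1 | 4.8% | 5.0% | 4.8% | 5.1% | 5.0-5.1% |
| 1.25 | 6.4% | 6.6% | 5.7% | 5.9% | 4.9-5.0% |
| 1.5 | 7.4% | 7.9% | 6.5% | 6.8% | 5.0-5.1% |
| 2 | 8.7% | 9.0% | 7.7% | 8.0% | 5.0-5.1% |

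A repeat simulation gave 6.5, 7.6 and 9.1% (both) and 6.1, 6.9 and 8.1% (only NSAP) for k = 1.25, 1.5 and 2. At k = 1.1 the formula gives 5.5% (both) and 5.2% (only NSAP).

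**All three means equal.** The three-group step keeps the NSAP-radiculopathy rate at 2.3% for k = 1 and at 3.2-4.6% for unequal SDs with k up to 2. There is no excess.

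**NSAP-control power.** The difference is 0.5 times √((k² + 1)/2), and the radiculopathy mean equals the NSAP mean:

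| k | Both: SNK / gated Welch | Only NSAP: SNK / gated Welch |
|---|---|---|
| 1 | 62.4% / 63.2% | 62.3% / 63.0% |
| 1.25 | 59.6% / 64.6% | 65.9% / 65.8% |
| 1.5 | 57.2% / 65.4% | 68.8% / 67.6% |
| 2 | 54.3% / 66.3% | 72.9% / 69.3% |

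The loss, about 5, 8 and 12 points, appears only when both patient groups are more variable. With radiculopathy twice as far from controls as NSAP, it is about 2, 4 and 6 points. In the NSAP-only case the apparent gain reflects a test that is slightly too liberal.

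**The hypothesised mixture itself.** Let a share p of NSAP resemble radiculopathy and the rest resemble controls, with the two D control-SDs apart. The NSAP SD is √(1 + p(1 − p)D²): for p = 0.5 this is 1.03 at D = 0.5, 1.12 at D = 1 and 1.41 at D = 2. The NSAP mean then lies (1 − p)D from radiculopathy. At p = 0.5 and D = 1, NSAP-control power is 67.1% with SNK and 65.6% with unadjusted Welch tests.

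**The case against.** The strongest reply is that this is a condensed article. Variance checks, transformations and fallback tests are commonly left to the full plan, and pooled-variance ANOVA with equal groups is conventional. This stands in part: the lack of a variance check is not a finding. What remains is that the article does name a post-hoc method, and a more robust one is available.

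A reader might infer that the plan's own hypothesis makes both patient groups more variable than controls. It does not. It concerns NSAP only, and only as a possibility. The Discussion describes radiculopathy as the better-defined group, selected on clinical tests and MRI. Extra spread there is an inference from unstated root levels and fixed test sites.

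A reader might also infer that NSAP-control power must suffer. That needs both patient groups to be more variable; otherwise the direction reverses.

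Finally, a mixture of radiculopathy-like and control-like patients differs in mean from a homogeneous radiculopathy group, so rejecting equality would be correct, not a false positive. This also stands. The excess error needs equal means with unequal spread, which can occur if radiculopathy is itself mixed at a site or if NSAP is more variable for another reason.

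**Conclusion.** The point holds as a conditional robustness weakness. The named test pools one variance over three groups, and equal groups of 50 do not protect its pairwise comparisons. With equal patient-group means, clearly different controls and assumed SD ratios of 1.25 to 2, the NSAP-radiculopathy false-rejection rate is about 6-8% (only NSAP more variable) or 6.5-9% (both patient groups) instead of 5%. Near a ratio of 1.1 the excess is negligible, and with all means equal it is absent.

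The article gives no SDs, so it neither confirms nor rules out ratios of this size. It does not support saying that both patient groups will be more variable, or that NSAP-control power will necessarily be lost.

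**What to change.** Replace the sentence on continuous data with: *Welch's one-way ANOVA; if significant, pairwise Welch t-tests with 95% confidence intervals (or Games-Howell).* With exactly three groups, pairwise tests made only after a significant overall test still control the family-wise error for each outcome.

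The cost is one sentence and standard software. Under equal variances, NSAP-control power is 63.2% against 62.4% for Student-Newman-Keuls when the two patient means coincide, and 69.7% against 69.9% when radiculopathy lies twice as far from controls. These figures are for the gated Welch tests. Games-Howell applies the three-group critical value to every pair, so it is more conservative, and its power was not calculated here.

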### Study Limitations

• The screening, group allocation and data collection will all be carried out by the principal investigator. Whilst independent screening and group allocation would be preferable, this is not feasible. The authors acknowledge the bias inherent in this.

• NSAP participants could be investigated with MRI and/or nerve conduction studies to rule out any identifiable nerve dysfunction and the authors acknowledge this limitation.

## Discussion

### Scientific significance

WRULD are a significant public health problem and NSAP constitutes a diagnostic category for which our understanding of pathophysiological mechanisms remains unclear. The spectrum of clinically suspected neuropathic pain ranges from more obvious conditions such as trigeminal neuralgia to those with vague signs of nerve disorder such as NSAP. A thorough description of the somatosensory profiles of NSAP patients and a comparison with a more defined group of patients with probable neuropathic pain will help in the understanding if underlying neurophysiology in this condition and may influence future classification and intervention studies relating to NSAP.

## Abbreviations

**WRULD**: Work related upper limb disorders; **NSAP**: Non specific arm pain; **QST**: Quantitative Sensory Testing; **PPT**: Pressure Pain Threshold; **LANSS**: Leeds Assessment of Neuropathic Symptoms and Signs; **ULNT**: Upper limb neurodynamic tests; **DASH **Disabilities of the Arm; Shoulder and Hand; **TSK**: Tampa Scale of Kinesiophobia.

